### Participant outreach

#### Sample size

Two hundred and fifty English-speaking subjects will be recruited for this study globally, via online methods. The number of participants needed is based on an a priori power analysis using G^*^Power software (*F*-test, ANOVA: Repeated measures, within-between-interaction; 1− β = .80, α = .05, Cohen's f = .10), which revealed that the study would require a total sample size of *N* = 198 (Faul et al., 2007). An additional 52 participants have been added to this estimated sample size to account for an assumed 20% dropout rate.

#### Participant criteria

Participants will sign a consent form electronically stating that; (a) they are at least 18 years of age or of legal age in their country of residence, (b) they have not been clinically diagnosed with a disorder related to impulse control or addictions, (c) they express both a desire and difficulty to reduce their non-essential consumption, (d) they have not previously followed the social media trend of consumer Minimalism.

#### Recruitment methods

Participants will be recruited through convenience sampling via two main avenues; (a) social media posts in consumption related forums and sites as well as Facebook pages and groups, and (b) campus posters circulated around the universities of the research team. The main appeal to participants in all avenues will follow a “question and proposal” format, i.e., “Do you want to decrease your buying? Sign-up to try out an experimental treatment!” Each poster and online recruitment posting will feature a QR code that participants can scan with their smartphones to download the intervention mobile application. The consent form will be embedded in the in-take questionnaire.

#### Participant commitment through feedback

Efforts to promote continued participation will be aimed at both extrinsic and intrinsic motivation, with a primary emphasis on the latter. Two intrinsic, motivational aspects will be addressed in the recruitment call; (a) participants will be offered to try treatments that may help them with their reported, personal goal of reducing non-essential material consumption and (b) participants will receive feedback on their personal progress following the intervention.

To further motivate participants to remain in the study throughout the weeklong intervention, a lottery prize of 100 euros will be raffled to one participant who completed the full intervention. The winning participant will be able to receive this prize via either bank transfer or a donation made on their behalf to a charity of their choice.

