### Mobile application

A mobile application will be developed and used in the study for stimuli presentation, data collection, communication, and once the study is complete, a personalized progress report. Video stimuli will be embedded into Qualtrics questionnaires, which will be linked in the mobile application. This will allow participants to easily fill-out the questionnaires before and after viewing the video stimuli. Time spent viewing the videos will be recorded by a “timing” function in Qualtrics.

The mobile application push-notification system will remind participants to view the video and fill in a questionnaire on a daily basis throughout the weeklong intervention. Thus, participants will receive one push-notification a day, until the intervention is complete. The mobile application will also allow both the participants and research team to communicate via email. This will be useful if any problems or questions arise. Finally, users of the mobile application will receive a personalized progress report once the study is completed.

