After the intervention is completed, including a one-month follow-up, the research team will conduct initial analysis on the effectiveness of the employed interventions. Specifically, conducted analysis will test whether either one or two of the employed interventions prove to be beneficial in reducing excessive consumption and increasing well-being, in comparison to the control condition. If one or both interventions prove to be effective, they will be offered to participants who did not experience them while participating in the study. Thus, all participants will be afforded the opportunity to take part in an effective intervention for consumption reduction, should the research team identify one. Participants will also receive debriefing of the study and will be exposed to all three conditions employed in the study design.

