### Surveys and intervention

After baseline measurement is completed, participants in each intervention group will be requested to watch one video per day for six days, and answer a short questionnaire following each video. The videos will be between three and five minutes long and consist of a young, female presenter, talking to the camera as if talking to an audience.

The main content of the videos in both intervention conditions will be identical. However, the opening and closing sections of each video will be filmed separately, and emphasize either self-transcendence or self-enhancement values and goals, per condition. For example, in the self-transcendence condition the presenter will say, “We are here because we want to *make the world a better place*. By being *environmentally friendly, conscience* and *ethical*, we can *make a positive impact on the world*.” Conversely, in the self-enhancement condition, the presenter will say, “We are here because we want to *make our lives better*. By being *less stressed, more in control*, and *spending wisely*, we can *make a positive impact on our own lives*.” Moreover, visual stimuli integrated into the videos will prime participants of either self-transcendence, biospheric values (e.g., gardens, lakes, plants) or self-enhancement, hedonic and egoistic values (e.g., friends chatting and drinking coffee together). In the control condition, there will be no intervention, but participants will be pinged by the mobile application to answer a survey once per day for six days. Follow-up measurements will be conducted via web-site one month after the last intervention day for all three groups.

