## Materials and equipment

### Smartphone application

The smartphone application will contain four key features:

Questionnaires: the mobile application will link participants to Qualtrics questionnaires, including video stimuli. These will be presented to the participants at in-take, during the daily intervention, and at post-intervention assessment;Notifications: a push-notification system will remind participants to view the stimuli and complete the questionnaires every day, while the intervention is in progress;Communication with the research team: an email link will allow participants to contact the research team directly;Personalized progress reports: participants will receive a link to a report of their post-intervention progress once the study is complete.

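### The raffle and push reminders are confined to the intervention week, and raffle entry rewards completing the intervention rather than giving outcome data, so the one-month follow-up rests on weak motivators

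*Protocol article*

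**What the plan says.** All references are to the protocol article.

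- **Prize.** Participant commitment through feedback gives its purpose: "To further motivate participants to remain in the study throughout the weeklong intervention". The rule is that "a lottery prize of 100 euros will be raffled to one participant who completed the full intervention".
- **Reminders.** Mobile application: "participants will receive one push-notification a day, until the intervention is complete". Smartphone application repeats the limit, with reminders to "complete the questionnaires every day, while the intervention is in progress".
- **Questionnaires in the app.** Smartphone application: "These will be presented to the participants at in-take, during the daily intervention, and at post-intervention assessment".
- **Follow-up.** Surveys and intervention: "Follow-up measurements will be conducted via web-site one month after the last intervention day for all three groups". No prize or reminder is attached to it.
- **Role of t_end.** Procedure has the dependent variables measured again at t_end. The behaviour analysis states an expectation for the t0 to t_end effect. Ethics process says: "After the intervention is completed, including a one-month follow-up, the research team will conduct initial analysis on the effectiveness of the employed interventions".
- **Load by arm.** The video arms watch one video of three to five minutes on each of six days, with a short questionnaire after each. For control, "In the control condition, there will be no intervention"; they answer one survey a day for six days.
- **Other motivators.** Participants are promised feedback on their progress, delivered through the app when the study ends. After the one-month follow-up, any intervention found effective is offered to those who did not receive it.
- **Allowance.** Sample size gives 198 required and 52 added for an assumed 20% dropout, 250 in all. It does not say whether the 20% runs to t7 or to t_end.

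**The concern.** An incentive shapes the data that it rewards. This one rewards exposure to the intervention, whereas the trial needs outcome data from everyone randomised, including people who stop watching. A video-arm participant who stops partway through the week loses the raffle entry, and with it the only material reason to answer t7. After t7 the raffle has no further effect on anyone, and the reminders have ended just as the longest interval in the study begins.

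Two things are at stake. First, missing outcomes may become linked to adherence, and adherence plausibly tracks motivation to cut consumption. Because the same rule is harder to satisfy in the video arms than in control, loss may also differ by arm. Second, the persistence result at t_end may rest on far fewer people than the sample size assumed. Analysis cannot recover follow-up data that were never collected.

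**Working it through.** **1. The plan's own sample size.** The article gives f = 0.10, alpha 0.05, power 0.80 and N = 198 for the within-between interaction of a repeated-measures ANOVA. It does not give the number of groups (k), number of measurements (m) or correlation (rho) that were entered, so those are my assumptions. With sphericity:

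- lambda = f² × N × m / (1 − rho)
- df1 = (k − 1)(m − 1); df2 = (N − k)(m − 1)

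k = 3, m = 3, rho = 0.5 needs N = 202, within about 2% of 198. k = 3, m = 2, rho = 0.6 needs 196, or 198 in equal groups. k = 3, m = 2, rho = 0.5 needs 244. The stated figure is reproducible under a plausible setting, and I use the first one below.

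**2. The dropout allowance.** 198 / (1 − 0.20) = 247.5, so 248; the plan recruits 250. In the other direction, 250 × 0.80 = 200, which is two more than required. The largest loss that still leaves 198 is 52 / 250 = 20.8%.

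**3. What higher loss at t_end would do.** The article gives no loss figure for t_end, so every rate above 20% is an assumption. Power is for f = 0.10, k = 3, m = 3, rho = 0.5.

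| Loss by t_end | Remaining of 250 | lambda | Power | Recruits needed to keep 198 |
|---|---|---|---|---|
| 20% | 200 | 12.0 | 0.80 | 248 |
| 30% | 175 | 10.5 | 0.73 | 283 |
| 40% | 150 | 9.0 | 0.66 | 330 |
| 50% | 125 | 7.5 | 0.56 | 396 |

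These powers apply to an analysis of people with all three measurements. A t0 to t7 comparison is affected only by loss at t7.

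**4. Differential loss.** Let p be the share lost in an arm and d the amount, in SD, by which those retained do better than those lost. The bias in the video-control difference is then p(video) × d(video) − p(control) × d(control). None of the four terms is in the article. As an illustration only, take 30% lost and d = 0.3 SD:

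- selection in the video arms only: 0.30 × 0.3 = +0.09 SD
- selection in control only: −0.09 SD
- equal selection in both: 0

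The sign depends entirely on which arm loses its less motivated members.

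**The case against.** Several points on the other side stand.

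- **Follow-up is not without any means of retention.** A reader might infer that it is, because prize and reminders both end with the week. But the section on participant commitment puts its main weight on intrinsic motivators, one of which is the progress report, delivered at the end of the study with no stated condition on finishing the videos. The offer of an effective intervention also comes after t_end. Both are weak for this purpose: neither is stated to depend on answering t_end, and the offer is an ethics measure that applies only if an intervention works.
- **Controls are not shut out of the raffle.** Read alone, "In the control condition, there will be no intervention" might suggest that they have nothing to complete. The article uses the word intervention for the week in all arms, and even gives all three groups a last intervention day, so controls plausibly qualify.
- **People who stop watching do reach t_end.** The note to Figure 1 and the follow-up text place t7 and t_end by the study week, not by personal adherence. Nothing says that such people lose reminders during the week or are not followed up.
- **The app may carry t_end.** The values analysis counts t7 and t_end as two post-intervention measurements, so the app's post-intervention assessment could include both. The point does not need this limb.
- **The prize is small.** 100 euros among about 200 completers is 0.50 euro each in expectation, so redirecting it may change little by itself.
- **Direction of bias.** People drawn by an advertised treatment and then given only mood surveys may leave control, which would leave that arm with its most motivated members.

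How the follow-up invitation is sent could also be left to a fuller protocol. The raffle rule and the end point of the reminders could not: the article states both.

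**Conclusion.** The point holds as a cheap improvement. The raffle depends on completing the intervention rather than on supplying outcome data, and both the raffle and the push reminders are confined to the intervention week. The t_end measurement therefore rests on motivators that are not tied to answering it. With a heavier task in the video arms, the rule can link missing t7 and t_end data to adherence and make loss unequal between arms.

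Size: the single 20% allowance leaves 200 against 198, so there is almost no room for extra loss at t_end. At 30% to 50% loss, power would be about 0.73 to 0.56. Those loss rates are assumed, as are the three groups, three measurements and correlation of 0.5.

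A reader might go further and conclude that the missing data bias the comparison toward benefit. The article does not support this. The 0.09 SD illustration takes either sign, and all its inputs are assumed.

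**What to change.** - **Participant commitment through feedback:** enter into the same 100 euro raffle every randomised participant, in any arm, who submits both the t7 and the t_end questionnaires, however many videos were watched. Draw it after t_end.
- **Mobile application and Smartphone application:** add a push notification for t_end, with one repeat, sent through the installed app to everyone randomised, including those who stopped watching.

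Cost: the prize money and the app are unchanged. The work is a few wording changes and one or two extra notifications per person. The draw comes about a month later, and the incentive to watch every video is slightly weaker. The change should be in place before recruitment, since the raffle terms are part of what participants are told.

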### Surveys and intervention

After baseline measurement is completed, participants in each intervention group will be requested to watch one video per day for six days, and answer a short questionnaire following each video. The videos will be between three and five minutes long and consist of a young, female presenter, talking to the camera as if talking to an audience.

The main content of the videos in both intervention conditions will be identical. However, the opening and closing sections of each video will be filmed separately, and emphasize either self-transcendence or self-enhancement values and goals, per condition. For example, in the self-transcendence condition the presenter will say, “We are here because we want to *make the world a better place*. By being *environmentally friendly, conscience* and *ethical*, we can *make a positive impact on the world*.” Conversely, in the self-enhancement condition, the presenter will say, “We are here because we want to *make our lives better*. By being *less stressed, more in control*, and *spending wisely*, we can *make a positive impact on our own lives*.” Moreover, visual stimuli integrated into the videos will prime participants of either self-transcendence, biospheric values (e.g., gardens, lakes, plants) or self-enhancement, hedonic and egoistic values (e.g., friends chatting and drinking coffee together). In the control condition, there will be no intervention, but participants will be pinged by the mobile application to answer a survey once per day for six days. Follow-up measurements will be conducted via web-site one month after the last intervention day for all three groups.

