## Objectives

The project will test whether user-generated content promoting either self-transcendence or self-enhancement values and goals could be effective in reducing excessive consumption, as well as increasing well-being. The effectiveness of the interventions will be tested by measuring their effects on life-satisfaction, intent to adopt voluntary simplicity, and purchasing intent and behavior. The project's main research questions are:
Could user-generated content promoting voluntary simplicity reduce excessive consumption?Are self-enhancement goals as effective in promoting sustainable behavior as self-transcendence goals, in user-generated Minimalism content?

We are also interested in whether exposure to user-generated content promoting voluntary simplicity affects one's well-being. Finally, the relationship between one's intent to reduce consumption and one's consumption behavior might generate meaningful insights.

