### Video checklists

Video checklists describe the key concepts and behaviors to be addressed in the video stimuli. These checklists detail the following stimuli requirements, per condition:
Content: information conveyed (stable across intervention conditions)Condition priming: what values and goals will be primed in the opening and closing statements of the videos, as well as the visual stimuli (self-transcendence vs. self-enhancement)Style: the presenter's tone and expression (stable across intervention conditions).

Due to internal reliability concerns, one presenter will appear in all videos, for both intervention conditions. The presenter will be a female in her twenties, similarly to many Minimalism vloggers. Appendix A presents an example of a video checklist.

The research team will contact several social and consumer psychologists to review these checklists and approve that they (a) prime self-transcendence and self-enhancement values and goals, per condition, and (b) promote consumption reduction, prior to video creation.

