### Video pre-testing

The videos will be pretested in a convenience sample of international psychology students at the advanced undergraduate and graduate level. We aim to test the face validity of the videos. Thus, the pre-test population will consist of young consumers with a basic scientific knowledge on motivation, values, and goals. The pre-test sample will therefore be slightly different from the population addressed in the main study. Participants will watch subsets of videos from both intervention conditions and rate the face validity of the videos (e.g., “Did the presenter promote biospheric values?”, “Did the presenter promote egoistic values?”). They will also note any manipulation concerns or potential confounds in the video stimuli of both conditions. Additionally, participants will rate how entertained, focused and interested they were when watching the videos. The latter measures will be used to estimate main-study participants' motivation in watching the daily video stimuli during the weeklong intervention. If a video receives a low score on either validity or entertainment value during the pre-test, the research team will revise the videos based on pre-test comments, and re-test them on a similar sample.

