##### Assessment of Consumption Related Attitudes and Behaviors

*Shopping intention*. Shopping intention will be measured by adapting the three items of the eight-point semantic scale of behavioral buying intention (Baker and Churchill, 1977). The original items were intended to measure participants' intention to buy a specific product. In this study, the items will be adapted to suit the context of the non-essential product buying intention. Participants will be asked to think of a type of product they would normally buy, which is non-essential (e.g., clothing, sweet snacks, coffee). Then, they will be asked about their purchase intent for this product, for example: “Would you buy this non-essential product within the next seven days?” In response to the question, participants should indicate their intention on an eight-point semantic scale of “yes—definitely” to “no—definitely not.”

*Buying frequency and behavior*. Two questionnaires (see Appendix B) measuring shopping frequency (Section A, seven items) and average weekly non-essential expenditures (Section B, two items) will be administered to participants. The order of the items within both sections will be randomized. Responses for five of the total nine items of the two questionnaires will be given on a six-point Likert scale, ranging from zero to five (e.g., “How likely are you to shop for something you need in the coming week?”) that will be averaged within each section. The remaining four items will require an open response by the participant (e.g., “How many times do you typically go shopping in a week?”).

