**Figure 2 F2:**
[figure not shown]
Proposed pattern of results showing reduced consumption within experimental groups.

The strength of the effect is expected to be higher between t0 and t7 than between t0 and t_end_. In other words, we expect a stronger effect during the intervention compared to the post-intervention phase. Condition will be contrast coded to facilitate the interpretation of the interaction (Cohen et al., 2013). This analysis will also be used to examine which aspects of user-generated content affect excessive consumption, comparing self-transcendence to self-enhancement conditions. Although, there is no clear expectation on which content will have a stronger effect, this will be examined through exploratory analyses. Participants' in-take reported motivations, values, involvement, and personal goals to reduce consumption will be considered as control variables in these analyses.

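### The only example of self-enhancement imagery shows use of a product that the shopping-intention outcome names as non-essential, so a difference between the two video arms could reflect a consumption cue as well as the primed values

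*Protocol article*

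**What the plan says.** Under Surveys and intervention, the protocol states that "The main content of the videos in both intervention conditions will be identical". The openings, closings and integrated visual stimuli differ by condition. For one arm the visuals are to prime "self-transcendence, biospheric values (e.g., gardens, lakes, plants"; for the other, "self-enhancement, hedonic and egoistic values (e.g., friends chatting and drinking coffee together". The coffee scene is the only example given for the self-enhancement arm.

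Video checklists describes the intended difference between the arms as "what values and goals will be primed in the opening and closing statements of the videos, as well as the visual stimuli". Content and presenter style are to be held stable.

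Under Assessment of Consumption Related Attitudes and Behaviors, shopping intention is rated for a product that participants normally buy, "which is non-essential (e.g., clothing, sweet snacks, coffee". Coffee is thus one of three printed prompts for this outcome.

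Objectives lists as its second main question: "Are self-enhancement goals as effective in promoting sustainable behavior as self-transcendence goals, in user-generated Minimalism content". The Proposed analysis (text after Figure 2) addresses it by "comparing self-transcendence to self-enhancement conditions". It states no directional expectation and calls the analysis exploratory.

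**The concern.** The two video arms are built to differ in the values and goals primed and in nothing else, so that a difference in outcome can be attributed to those values. The example imagery brings in a second difference. One arm may see an agreeable scene of people using an item that the trial's own questionnaire offers as a non-essential purchase. The other arm's examples contain no product.

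The second main question is at stake. If the arms differ on purchase intention, the data could not show whether the values or the product imagery produced the difference. If they do not differ, a real effect of values could have been offset by the cue. The background sections already cite literature in which self-enhancement values go with less sustainable behaviour. A poorer result in that arm would therefore be easy to accept as confirmation.

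**Working it through.** The plan gives no figure to reproduce here. The check sets the sections side by side.

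1. **Overlap of stimulus and outcome.** Coffee appears in the self-enhancement example (Surveys and intervention) and among the prompts for the non-essential product (Shopping intention). The self-transcendence examples name no product. The overlap is in the text.

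2. **Can the analysis remove it?** The cue would be delivered with the arm, so randomisation does not balance it. The regression adjusts for baseline outcome, values and demographics, and the cue comes after all of these. The manipulation check (Changes in values and motivations) measures values and motivations. It could succeed in both arms while a consumption cue was also acting.

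3. **Do the safeguards catch it?**
   - Video checklists: outside psychologists approve that the checklists prime the intended values and promote consumption reduction. Neither criterion asks whether the two arms' visuals are matched on product content.
   - Video pre-testing: of the raters, the protocol says "They will also note any manipulation concerns or potential confounds in the video stimuli of both conditions". Revision, however, is tied to a low score on validity or entertainment. A pleasant, plausibly hedonic coffee scene could score well on both, and a noted confound does not by itself lead to a change.
   - The sample checklist in Appendix A is not in the text at hand and could not be checked.

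4. **Which comparisons are touched?** Let *s* be the unknown shift, of either sign, that the cue causes in the self-enhancement arm's mean.
   - Self-enhancement minus self-transcendence: moves by *s*.
   - Equal-weight mean of both video arms minus control: moves by *s*/2. The equal weights are an assumption, because the protocol announces contrast coding without giving weights.
   - Self-enhancement minus control: moves by *s*. That comparison asks whether the videos as delivered work, so the imagery is part of the treatment tested.

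   The problem of attribution therefore lies mainly in the two-arm comparison.

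5. **How large could *s* be?** The protocol gives nothing to estimate it. Purely as an assumption, suppose 10% to 30% of participants name a product of the kind shown, and the cue moves their intention by 0.25 to 0.5 SD:
   - lower end: 0.10 × 0.25 = 0.025 SD
   - upper end: 0.30 × 0.5 = 0.15 SD

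   As a rough yardstick, the planning value f = .10 would correspond to 2 × 0.10 = 0.20 SD between two equal groups. The plan applies f to a within-between interaction, so the comparison is loose. Both inputs are invented for illustration, and an incidental image moving intention by more than the 0.20 SD yardstick is generous.

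**The case against.** The strongest reply is that this builds a lot on one illustrative phrase. Four stronger readings are tempting, and the documents support none of them.

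- **Exposure on every day of the intervention.** A reader might infer that the self-enhancement arm sees coffee drinking in all six videos. The protocol gives a single example for videos still to be made. It does not say that the scene recurs, or that it will be in any final video.
- **A bias against the self-enhancement arm.** This is plausible but not established. The scene shows drinking, not buying. The same arm's script encourages wise spending, and both arms teach consumption reduction. The Voluntary simplicity section describes replacing non-essential goods with non-material elements of life. Time with friends could be read as one of these, so the image could even favour that arm.
- **People versus no people as a separate confound.** The protocol does not say that the nature scenes exclude people, and the same presenter appears in all videos. A contrast between personal enjoyment and nature is largely the intended value contrast.
- **A broad effect on the trial's outcomes.** Participants name their own product, so the overlap is direct only for those who choose coffee or something similar. Shopping intention is one of several outcomes. Shopping frequency and weekly spending have their own items.

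It is also fair to say that expert review and pre-testing offer partial protection and that the two-arm analysis is labelled exploratory.

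These points limit the size and certainty of the concern. They do not remove it. The coffee scene is the only guidance given for this arm's visuals, and no stated criterion requires the arms to be matched on product content. Exploratory status does not make a confounded contrast interpretable, and Objectives lists the question as a main one.

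**Conclusion.** The concern holds in a limited, conditional form. If imagery like the stated example is used, a difference in purchase intention between the two video arms could reflect a consumption cue as well as the primed values, and the planned analysis could not tell these apart. The size and direction are unknown. The 0.025 to 0.15 SD range rests wholly on assumed inputs and is not evidence of bias. The pooled comparison of videos with control is less affected. The conclusion rests on two assumptions: that the example indicates what will be filmed, and that seeing a product used can affect the intention to buy it or similar items. The change is worth making because it is cheap before filming, and the difference cannot be adjusted away afterwards.

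**What to change.** Before filming:

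1. In Surveys and intervention, replace the coffee example with hedonic or egoistic imagery that shows no outcome-type product, such as friends chatting or walking together without one. The replacement should also not show a result of the taught behaviours. A tidy, decluttered room in one arm only would add an opposite cue.
2. In Video checklists, add that the condition-specific visuals in either arm show no purchase or use of non-essential products, and that their screen time is matched across arms. Limit the rule to these visuals, so that the shared tutorials on decluttering and donating stay as they are.
3. In Video pre-testing, have raters score consumption cues in each arm's videos, and let a noted imbalance trigger revision alongside low validity or entertainment scores.

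The cost is a slightly narrower choice of hedonic imagery, a few extra pre-test items, and possibly a re-edit if an imbalance is found. The main study needs no additional participants or procedures.
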